##### Phase 3 – maintenance (Months 13–18)

During the last 6 months, participants are expected to be self-managing exercise and maintaining adherence to 150 minutes of moderate intensity exercise each week. Exercise diaries are submitted weekly, and the coach calls a subject to schedule a face-to-face interaction if relapse occurs during this phase. See Figure 1 for a depiction of the Study Model.

**Figure 1 Fig1:**
[figure not shown]
**Study model.**

#### Standard care

Given that the HFSA recommends 150 minutes of moderate intensity exercise per week, it would be unethical to ask the control group to abstain from exercise. The SC group is provided access (free membership) to the exercise facility and regular facility staff during the 18 month study period. This membership was provided in order to control for access as a potential confound to adherence since this is noted as a common barrier to exercise adherence [53, 54]. During all three phases of the study, participants in both groups are expected to record all moderate intensity exercise on a weekly diary and wear the heart rate monitor during this exercise. The investigators recognize that the HC intervention group will receive more attention than the SC group; however, more contact between participants and interventionists and face-to-face encounters versus other methods of intervention delivery have been documented to produce larger effects and thus are being evaluated as part of the intervention [47, 52]. Both the HC intervention group and the SC group receive usual care for heart failure from the participating institutions. Subjects from both groups are instructed not to participate in group exercise classes or education offerings by the exercise facility.

### Procedures for intervention fidelity

Procedures to evaluate intervention fidelity are incorporated into the design of the study. The intervention fidelity plan addresses the training of those interacting with the participants, the delivery of the intervention, and the receipt and enactment of the intervention for the participants. Training sessions focused on consistency between sites and personnel. Standardized training manuals and scripts were used for training sessions of study personnel prior to the enrollment of participants. Booster training sessions occur every 6 months for data collectors and group session leaders and every 8–12 weeks for exercise coaches during the study. Delivery of the intervention by exercise coaches is scripted and actual delivery of the intervention components and length of the session are recorded each week in a database. This database is audited for adherence to the intervention and feedback is given to coaches at their meetings. Coaching sessions are video-recorded every few months to assess adherence to delivery of the intervention according to protocol. Group education session content is standardized with a pre-recorded video presentation followed by group discussion. Group session leaders fill out a self-report each session to document the discussion topics that were covered. Receipt and enactment of the intervention by participants in the HEART Camp group is gauged with exercise diaries, documentation from coaches, qualitative interviews, input and engagement surveys, receipt of intervention tools, and adherence to the exercise.

### Study outcomes and data collection

Table 3 describes data collection time points as well as outcome variables and measures specified by research aim. All questionnaire data is collected by interview according to standardized scripts and entered directly into an electronic database (REDCap) by the blinded research assistant [55]. The primary outcome of adherence is obtained through self-reported exercise diaries and validated by heart rate monitor (Polar Electro Inc., Lake Success, NY) data. All subjects are instructed to complete the diary and wear the heart rate monitor for each exercise session. Exercise coaches collect diaries and data from HC intervention participants during weekly coaching sessions and research personnel collect this data for the SC subjects by appointment every two months. Subjects are contacted by phone and diary information is collected by scripted interview if sessions or appointments are missed. Research assistants blinded to group assignment collect data on measures of physical function, psychological function, symptoms and quality of life (6 MWT, PROMIS-29, Dyspnea/Fatigue Scale and KCCQ), as well as measures related to the intervention mechanisms (knowledge, attitude, self-efficacy, self-management, and social support) at 6, 12 and 18 months (see Table 2).

**Table 3 Tab3:** **Outcome measures and data collection time points by research aim**

Variable	Measure description (data collection time points)
	**Baseline & screening**
**Demographic and clinical variables Tool**	Demographic (e.g., race, gender, age, marital status)
	Clinical data (e.g., ejection fraction or EF, medications, BMI, comorbidities)
**Cardiopulmonary stress test**	Determine suitability for exercise (no significant ischemia or arrhythmias)
	Heart rate ranges and appropriate levels of exercise training
	**Primary outcome – Aim 1 (Baseline, 6, 12 and 18 months)**
**Adherence**	
**Self-report**	**Exercise diary** for self-report of sessions per week and minutes per session [56]
**Heart rate monitor**	**Heart rate monitor** (used as validation of self-reported exercise each week
	**Evaluation of intervention mechanisms – Aim 2 (Baseline, 6, 12 and 18 months)**
**Knowledge**	**Physical activity & heart disease I.Q.** – developed by NHLBI [57] 12 true/false items testing knowledge of how physical activity affects the heart
**Attitudes**	**Attitudes toward physical activity/exercise** - 8 items measure negative attitudes toward physical activity and 6 items measure positive attitudes toward physical activity [58]
**Self-efficacy**	**Barriers Self-Efficacy Scale (BARSE) –** 13 item scale measures self-efficacy or confidence in exercise behavior [59];
**Self-management**	**Physical Activity Self-Regulation Scale (PASR 12)**
	Self-monitoring (2 items), Goal setting (2 items), Eliciting social support (2 items), Reinforcements (2 items), Time management (2 items) and Relapse management (2 items) [60]
**Social support**	**Revenson Support Scale**
	Problematic support (4 items) and Positive support (16 items) [61]
	**Health outcomes – Aim 3 (Baseline, 6, 12 and 18 months)**
**Physical function**	**6 Minute Walk Test (6 MWT) –** Objective measure of functional capacity (sub-maximal). Distance walked in 6 minutes [62, 63]
**Psychological function**	**PROMIS-29 Profile v1.0:** Anxiety (4 item subscale), Depression (4 item subscale), Satisfaction with Social Role (4 item subscale) [64]
**Symptoms**	**Dyspnea/Fatigue Scale –** Measures the magnitude of the task that evokes dyspnea or fatigue, the magnitude of the pace at which the task is performed, and the associated functional impairment in general activities as a result of the symptoms [65]
**Quality of life**	**Kansas City Cardiomyopathy Questionnaire (KCCQ) –** 23-item disease-specific measure of quality of life in heart failure [66, 67]
	**Qualitative data – Aim 5**
**Open-Ended questions**	All subjects complete at **baseline**
**All subjects at baseline**	Survey prior experience with exercise, expectations related to exercise and outcomes from participation
**Open-ended comments on exercise diaries**	All subjects complete **each week** of the study
**All subjects each week**	What helped you to exercise this week? What made exercising a challenge this week? Other comments?
**One-on-one interviews**	Open-ended questions with probing (30 minutes)
**with HC subjects**	Interviews completed at **3, 6, 12 and 18** months
	Survey subjects’ perceptions of their experience with exercise adherence (e.g., challenges with adherence, helpful strategies, difficulties)
**One-on-one interviews with coaches**	Open-ended questions with probing (**every 6 months during active recruitment**)
	Questions about perceptions of exercise adherence experiences, strategies/difficulties working with patients, assessments of intervention components, descriptions of the intervention process for each phase
**One-on-one interviews with group session leaders**	Open-ended questions with probing (**every 6 months during active recruitment**)
	Questions about perceptions of exercise adherence experiences, strategies/difficulties working with patients, assessments of intervention components, descriptions of the intervention process

Qualitative data is obtained from all study participants at baseline testing with an open-ended questionnaire exploring perceptions of prior experiences with exercise, expectations related to exercise and outcome expectations from participation in the study (see Table 2). Additional qualitative data is collected from open-ended questions on the exercise diary of what helped with exercise and what made exercise a challenge during the week, as well as a general comment section. The baseline questionnaire and all comments from the diaries are transcribed and used to supplement the thematic analysis of the qualitative interview data. Participants in the HC intervention group complete qualitative interviews at 6, 12 and 18 months, as well as at 3 months to obtain participant perspectives during the adoption phase of exercise. Selected SC subjects (i.e., low adherers or high adherers) complete qualitative interviews at completion of the 18 month study period.

### Data analysis

Before proceeding with analysis, a careful descriptive study will be conducted to identify outliers and evaluate distributional assumptions of all variables. Primary analyses will be conducted consistent with the intent-to-treat paradigm, with each participant’s data analyzed according to group assignment. Patterns of missing data will be evaluated, and where assumptions are reasonable, analysis methods that accommodate partial cases such as mixed linear models or generalized estimating equations (GEE) will be used. For analyses requiring complete data, we will impute missing values using the EM algorithm or multiple imputation, as appropriate. To evaluate the central hypothesis, a one-tailed z-test will be used to compare the proportion of patients in each intervention group who are exercising on average ≥80% of the recommended 150 minutes per week at 18 months. A supplemental analysis will compare groups across the entire 18-month study period (testing main and interaction effects) on weekly minutes of activity at moderate or greater intensity and on specific health outcomes. Models of mediation and moderation of the effect of the intervention on adherence will be explored using regression methods.

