This paper presents the study protocol for a prospective randomized controlled trial that is currently in progress. The Heart failure Exercise And Resistance Training Camp (HEART Camp - HC) intervention group is compared to a SC exercise group. The central hypothesis is that the HC group will have significantly better adherence to exercise at 18 months than the SC group. Those in the HC group receive a multicomponent behavioral intervention to assist them in adhering to exercise. The intervention components of knowledge, attitudes, self-efficacy, behavioral self-management skills and social support are measured and will be tested as possible mediators of the effect of the intervention on adherence. The intervention is being carried out in two sites in the United States (i.e., Detroit, MI with a predominately African-American population and Lincoln, NE with a primarily Caucasian population of patients). Race, gender and age will be explored as potential moderators of the effect of the HEART Camp intervention on adherence. Finally a qualitative component will explore the perceptions and experiences that contextualize exercise adherence.

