### Sample size

The required sample size for the study was estimated to compare groups on the primary endpoint of adherence at 18 months. In the calculations, the level of adherence in the control group was set at 0.25, the level of crossover seen in HF-Action during the first year. Reported adherence in the HF-Action exercise group was 0.38 at 12 months and 0.36 at 18 months. Having only two sites in the current study should allow greater control over study implementation, which should increase adherence. We expect to achieve adherence of at least 0.50 in the HC intervention group based on an adherence level of 86% in our R15 trial during the three months after the active intervention phase of that trial. A one-tailed z-test of the difference in proportions of this magnitude would have power of 0.90 (α = 0.05) with a total sample size of 126 participants.

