### Subjects

We will recruit 246 patients (123 participants from each study site). Assuming that 10% might not meet the medical criteria for safe participation in the study and that 30% will fail to attend at least 6 of the 9 planned sessions during the run-in period, 148 subjects will be randomized. Using HF-Action’s 12-month dropout rate of 32% as a guide, an additional 15% attrition is assumed over the 18 months of the study, resulting in the final desired sample size of 63 per group (total N = 126) at 18 months.

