### Recruitment and enrollment

Two sites were chosen for their ability to recruit and enroll participants from a diverse geographic area: BryanLGH Heart Institute in Lincoln, NE and The Henry Ford Health System in Detroit, MI. The Lincoln site is a cardiology practice with 15 cardiologists. This site was used in our previous work and allowed us to successfully recruit participants in a pilot R15 study. Of the 42 participants included in that study, only one person was African American. The Henry Ford Health System with 82% African-American patients, was chosen for the second site specifically because of its access to underserved and ethnic minorities and its previous experience enrolling patients with HF in exercise trials. Combined, the two enrollment sites served 3,563 patients with HF in 2010 when this study was conceptualized.

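### The primary z-test is valid but uses neither site nor baseline predictors, and the exploratory race-moderator result can barely be separated from a site effect

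*Protocol article*

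**What the plan says.** Data analysis fixes the primary comparison: "a one-tailed z-test will be used to compare the proportion of patients in each intervention group" who reach the adherence threshold at 18 months. No stratification or covariate is named. The Sample size section uses the same test. There, "the level of adherence in the control group was set at 0.25" and "We expect to achieve adherence of at least 0.50 in the HC intervention group", and the test "would have power of 0.90 (α = 0.05) with a total sample size of 126 participants". The Subjects section plans equal recruitment of 123 per site and ends with 63 evaluable patients per group.

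For Aim 4, race is one of three exploratory moderators. The analysis is described in one sentence: "Models of mediation and moderation of the effect of the intervention on adherence will be explored using regression methods". No covariates are listed, so site is neither included nor excluded. The Background describes the sites as "Detroit, MI with a predominately African-American population and Lincoln, NE with a primarily Caucasian population of patients". Recruitment and enrollment gives 82% African-American patients in the Detroit health system and says of the earlier study, which used the Lincoln site: "Of the 42 participants included in that study, only one person was African American".

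The article does not say whether randomization is stratified by site.

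**The concern.** Two separate matters arise.

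The first is efficiency. Coaches, group leaders and an exercise facility deliver the intervention at each of two sites whose populations differ, so adherence may differ by site. The number of run-in sessions attended (6 to 9 among those randomized) and baseline barrier self-efficacy (BARSE) may also predict later adherence. A crude comparison of two proportions uses none of this.

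The second is interpretation. If nearly all African-American participants are in Detroit and nearly all others in Lincoln, a race-by-arm term fitted without site takes up most of any difference between cities in how well the intervention works. A difference arising from coaching, facility or local population could then be reported as a racial difference in response.

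**Working it through.** **1. The plan's own figure.** Inputs from Sample size and Subjects: control 0.25, intervention 0.50, one-sided alpha 0.05, power 0.90, 63 per group. With pooled variance under the null and no continuity correction:

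n per arm = [1.645 × √(2 × 0.375 × 0.625) + 1.282 × √(0.25 × 0.75 + 0.50 × 0.50)]² / 0.25² = 62.3, rounded up to 63, so 126 in total. This matches exactly.

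Power at 63 per arm = Φ[(0.25 − 1.645 × 0.0863) / 0.0833] = Φ(1.297) = 0.903.

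**2. Adding site alone.** The documents give no between-site difference in adherence, so a range is assumed. Take two equal sites with 31.5 patients per arm per site, a constant arm difference of 0.25, and site rates g/2 above and below the plan's rates. The stratified difference is the equally weighted mean of the two site differences. Its variance is the sum over sites of the two arm variances, divided by 4.

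| Assumed site difference g | Power, site-stratified | Gain over 0.903 (points) |
|---|---|---|
| 0 | 0.903 | 0 |
| 10 points | 0.906 | 0.3 |
| 20 points | 0.914 | 1.1 |
| 30 points | 0.928 | 2.5 |

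The comparator of 0.903 is the crude test under simple randomization. If randomization were stratified by site, the crude test would be conservative: its true one-sided alpha would be 0.049, 0.045 and 0.040 at site differences of 10, 20 and 30 points.

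**3. Adding site and baseline covariates.** Approximate the effective sample size as 126 / (1 − R²), where R² is the share of variation explained. Values of 0.10 and 0.20 are assumptions, since the documents give none.
- R² = 0.10: 126 / 0.90 = 140, power 0.928.
- R² = 0.20: 126 / 0.80 = 157.5, power 0.951.

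**4. Overlap of race and site.** Inputs: 82% (Detroit health system) and 1/42 = 2.4% (earlier study), used as proxies for the enrolled mix, with equal sites. The overall African-American share is (0.82 + 0.024) / 2 = 0.422.
- Correlation: phi = 0.5 × (0.82 − 0.024) / √(0.422 × 0.578) = 0.81.
- Variance inflation: 1 / (1 − 0.65) = 2.86. The standard error of the race term grows by √2.86 = 1.69 once site is in the model.
- Share of a site-by-arm difference that would appear as race-by-arm if site is left out: P(Detroit given African American) − P(Detroit given not) = 0.972 − 0.156 = 0.82.
- If the Lincoln share were 10% (assumed): phi = 0.72, variance inflation 2.09, standard error inflation 1.45.

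**5. Patients who carry the separation.** With 63 evaluable per site, Detroit would have 63 × 0.18 = 11 non-African-American patients and Lincoln 63 × 1/42 = 1.5 African-American patients, each split over two arms. Almost all information that separates race from site comes from those 11.

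**The case against.** The crude z-test is a legitimate analysis of a randomized comparison and agrees with the sample-size calculation. Preferring an adjusted model is a choice, and the gain from site is small, or nil if the sites do not differ. All of that stands. A reader might infer that the omission leaves the trial short of power. The documents do not support this: power is 0.90 at their own rates. A power near 0.48 follows only if control adherence is set at 0.36, which the article reports for the exercise group of an earlier trial and does not use as its control rate.

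A reader might also infer that the plan leaves site out of the moderator model. It does not; it names no covariates at all, and an article may leave that list to a fuller document. Nor is it shown that chance site imbalance goes uncorrected, because the randomization method is not described.

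Aim 4 is exploratory, and Procedures for intervention fidelity describes training aimed at consistency between sites, scripted and audited coaching, and pre-recorded group content. A site difference need not therefore be a delivery difference; it could reflect the populations. Finally, the confounding comes from the choice of two sites. Adding site to the model exposes it but does not remove it. These points limit the finding to an improvement in efficiency and a caution on interpretation. They do not remove the overlap of race and site, which the article does not acknowledge.

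**Conclusion.** The primary analysis is valid and correctly sized, but makes no use of site or baseline predictors already collected. Adjustment is a modest improvement: about 0.3 to 2.5 points of power from site alone at assumed site differences of 10 to 30 points, and power of about 0.93-0.95 if all covariates explained 10-20% of the variation. The second range is purely an assumption, and attendance restricted to 6 to 9 sessions may predict less than hoped.

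The more consequential part is Aim 4. On the proxy shares, race and site correlate at about 0.81, and about four fifths of any site-by-arm difference would appear as race-by-arm if site were left out. It would go too far to say that race cannot be told from site at all, since about 11 evaluable Detroit patients provide some within-site contrast. It can barely be told. This rests on the 82% and 1/42 shares carrying over to enrolment and on equal sites at 18 months. With 10% at Lincoln the overlap is weaker but still strong.

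**What to change.** - Make the primary comparison adjusted, for example logistic regression on arm, site, run-in sessions attended and baseline BARSE, reported as a standardized risk difference with its confidence interval. Keep the crude z-test as supportive. Confirm that the baseline BARSE is taken before randomization, which the article does not state.
- In the race-moderator model, include site and site-by-arm. Show the within-Detroit race contrast descriptively, with its cell counts.
- State in the plan and in any report that race and site are largely confounded by design and that the exploratory race result can barely be separated from a site effect.

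The cost is wording and slightly more analysis work, with no new data and no change to the sample size. The downside is a much wider interval for the race moderator, about 1.45 to 1.7 times on the shares considered here.

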### Research design

This study uses a prospective randomized two-group repeated measures experimental design with four data collection points (baseline, 6, 12 and 18 months). This study also uses qualitative methods within the randomized control trial design to assess the context for exercise adherence in the intervention group [22–24]. Both the HC group and the SC group receive paid access (free membership) to an exercise facility over the 18 month study period and both groups receive usual care for heart failure from the participating institutions.

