**Table 1 Tab1:** **Inclusion and exclusion criteria for the HEART camp study**

Inclusion criteria	Exclusion criteria
• Diagnosis of heart failure	• Clinical evidence of decompensated HF
Stage C chronic HF	• Unstable angina pectoris
Confirmed by echocardiography and clinical evaluation)	• Myocardial infarction, coronary artery bypass surgery, or biventricular pacemaker less than 6 weeks prior
Either Heart Failure preserved Ejection Fraction (HFpEF) or Heart Failure reduced Ejection Fraction (HFrEF)	
• Nineteen years of age or greater	• Orthopedic or neuromuscular disorders preventing participation in aerobic exercise and strength/resistance training
• Able to speak and read English	• Participation in 3 times per week aerobic exercise during the previous 8 weeks.
• Telephone access in home (land line or cell phone)	• Cardiopulmonary stress test results that preclude safe exercise training
• Stable pharmacologic therapy per guidelines for past 30 days (i.e., stable doses of beta-blocker, ACEI or ARB, diuretic)	• Plans to move more than 50 miles from the exercise site within the next year
	• MVO2 in females >21 ml/kg/min and in males >24 ml/kg/min
	• Pregnancy - If participant is pregnant or plans to become pregnant during the study

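### The supplemental main-and-interaction analysis names no baseline adjustment; if baseline is a response level, the group main effect is three-quarters of the mean follow-up difference

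*Protocol article*

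**What the plan says.** Research design describes a "prospective randomized two-group repeated measures experimental design with four data collection points (baseline, 6, 12 and 18 months"). Table 3 heads the adherence rows "Primary outcome – Aim 1 (Baseline, 6, 12 and 18 months") and the health-outcome rows "Health outcomes – Aim 3 (Baseline, 6, 12 and 18 months"). Data analysis states the supplemental comparison in one sentence, which says that it will "compare groups across the entire 18-month study period (testing main and interaction effects"). The outcomes named there are weekly exercise minutes and the health outcomes. The sentence lists neither the time levels in the model nor any covariate. Mixed linear models and GEE are given as examples of methods that can use incomplete cases.

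The working hypotheses for Aims 1 and 3, under Study aims, name 6, 12 and 18 months and leave baseline out. The central hypothesis is tested separately, by a one-tailed z-test of proportions at 18 months.

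**The concern.** A two-group repeated-measures design with four times, combined with tests of main and interaction effects, reads most naturally as a group-by-time model with four levels. Baseline comes before the groups are treated differently, so its expected group difference under randomization is zero. A main effect over four levels averages that built-in zero with the three follow-up differences.

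This supplemental analysis is the only between-group comparison that the article states for Aim 3 (6-minute walk, PROMIS-29, Dyspnea/Fatigue, KCCQ) and for the over-time part of Aim 1. The sample was sized for the z-test alone, so power for these outcomes depends on how well the available data are used.

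**Working it through.** **The plan's own figure.** Sample size gives 0.25 versus 0.50, one-tailed 5%, power 0.90 and N = 126. With pooled variance under the null, n per arm = [1.645√(2 × 0.375 × 0.625) + 1.282√(0.25 × 0.75 + 0.50 × 0.50)]² / 0.25² = 62.3, so 63 per arm and 126 in total. This reproduces. It concerns only the z-test. The article gives no effect size, SD or correlation for the supplemental analysis.

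**Dilution of the main effect.** With differences d6, d12 and d18 at follow-up and 0 at baseline, the equally weighted four-time main effect is (0 + d6 + d12 + d18)/4. The follow-up mean is (d6 + d12 + d18)/3. The ratio is 3/4 whatever the correlation or the shape of the effect. For example, 0.2, 0.3 and 0.4 SD give 0.225 instead of 0.300.

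**Power.** My assumptions: n = 63 per arm, d = 0.4 SD at each follow-up, unit variance at every visit, the same correlation r between all visits, two-sided 5%, normal approximation.

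- Four-time main effect: effect 0.75d, variance 2(1 + 3r)/(4n).
- Three-time main effect, unadjusted: effect d, variance 2(1 + 2r)/(3n).
- Follow-up mean minus baseline (1 df): effect d, variance (2/n)[(1 + 2r)/3 + 1 − 2r].
- Group-by-time interaction over four times (3 df): noncentrality (n/2)d² × 3/[4(1 − r)].
- Baseline-adjusted follow-up mean: effect d, variance (2/n)[(1 + 2r)/3 − r²].

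At r = 0.6 the standard errors are √0.02222 = 0.149 (four-time main effect), √0.02328 = 0.153 (three-time), √0.01693 = 0.130 (change) and √0.01185 = 0.109 (adjusted). The ratios of effect to standard error are 2.01, 2.62, 3.07 and 3.67. The interaction noncentrality is 9.45.

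| Test | r = 0.5 | r = 0.6 | r = 0.7 |
|---|---|---|---|
| Four-time main effect | 0.57 | 0.52 | 0.48 |
| Three-time main effect, unadjusted | 0.79 | 0.75 | 0.71 |
| 3-df interaction | 0.63 | 0.73 | 0.86 |
| Follow-up mean minus baseline | 0.79 | 0.87 | 0.94 |
| Baseline-adjusted follow-up mean | 0.94 | 0.96 | 0.98 |

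**Sensitivity.** With an effect growing 0.2, 0.3, 0.4 SD and r = 0.6, the five rows become 0.33, 0.50, 0.58, 0.64 and 0.79. If correlation decays with distance between visits (0.5 between neighbours) and the effect is constant at 0.4 SD, they are 0.65, 0.82, 0.49, 0.60 and 0.87. At a neighbour correlation of 0.3, adjustment gains almost nothing over the unadjusted three-time test (0.91 against 0.90).

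**The case against.** The strongest reply is that the premise is inferred. Four data collection points are a measurement schedule, and Table 3 uses the same heading style for the mediators. The Aim 1 and Aim 3 hypotheses name only the follow-up visits. A three-visit model with baseline as covariate, or a mixed model with equal baseline means, would also fit the Data analysis wording, and a condensed article may leave that choice to an analysis plan that is not shown. This stands: a reader might infer that the article fixes baseline as an outcome level, but it does not, so the dilution is conditional. What remains is that the article commits to main and interaction tests without naming baseline adjustment. Adjustment improves on the unadjusted tests whether or not baseline is a response level.

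Other stronger readings also fail:

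- A reader might infer that baseline values are wasted or that every test is diluted. The interaction uses baseline as its reference, and the post-minus-baseline contrast keeps the full 0.40 SD. Its cost is efficiency.
- Setting 0.52 against 0.96 compares the worst test with the best and mixes two gains. At r = 0.6, removing baseline from the response takes power from 0.52 to 0.75; adjusting for it takes 0.75 to 0.96.
- The power figures do not carry over to weekly minutes. Table 1 excludes "Participation in 3 times per week aerobic exercise during the previous 8 weeks", so baseline minutes may be low with little spread. Equal variance and a correlation of 0.5 to 0.7 with follow-up would then be implausible.
- Dropping the group-by-time test would not be free of cost. Aim 1 predicts that the difference is largest at 18 months, and that test addresses it.

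**Conclusion.** The point holds as a conditional weakness in a supplemental analysis. If baseline is a response level, the group main effect is exactly three-quarters of the mean follow-up difference; this needs only equal weighting and equal expected baseline means. Under either reading, baseline adjustment is the more efficient use of the health-outcome data: 0.94 to 0.98 power, against 0.48 to 0.94 for the unadjusted tests, over correlations of 0.5 to 0.7. Those figures rest entirely on the assumed 0.4 SD effect, equal correlation and 63 per arm. The direction of the gain is firmer than its size, which shrinks at low correlation. A reader might infer that the trial's main conclusion is at risk. It is not: the 18-month z-test and N = 126 do not use this model.

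**What to change.** In Data analysis, specify for the Aim 3 health outcomes that 6, 12 and 18 months are the outcome times and that the baseline value of the same measure enters as a covariate. A mixed model with baseline means constrained equal between groups would serve as well. Report the adjusted group difference averaged over follow-up and at 18 months, and keep a group-by-time test over the three follow-up visits. If a four-level model is retained for any outcome, state that its group main effect is not the treatment-effect estimate.

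For weekly minutes, leave baseline out of the outcome times and expect little gain from adjustment.

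The cost is a few sentences. Table 3 already schedules the baseline health measures, so no new data are needed and the table can stay as it is.
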